## Abstract

**Background:**

Only a small fraction of individuals with pathological or problematic gambling seek professional help despite available evidence-based treatments such as cognitive behavioral therapy (CBT). Anonymous Internet-based interventions may help to overcome treatment barriers. Results of a pilot study using an Internet-based intervention for depression in a sample of individuals with problematic or pathological gambling behavior show that both depressive and gambling-related symptomatology can be reduced with a generic depression program compared with a wait-list control group. Based on encouraging results of the pilot study, we developed a low-threshold, anonymous and cost-free online self-help program (“Restart”) to test whether a program tailored to the needs of gamblers yields better results compared to the effects of the intervention evaluated in the pilot study. The online self-help program is based on CBT, targeting emotional problems and gambling-related symptoms and is accompanied by a smartphone application to sustain treatment benefits.

**Method:**

A randomized controlled trial with two conditions (intervention group and wait-list control group), two assessment times (reassessment after 8 weeks) and a total of 136 participants is planned. The primary outcome will be change in pathological gambling measured with the Pathological Gambling Adaptation of Yale-Brown Obsessive-Compulsive Scale from pre to post intervention. The change in depressive symptoms (assessed with the Patient Health Questionnaire - 9 depression module) and gambling-related dysfunctional thoughts (assessed with the Gambling Attitudes and Beliefs Survey) will represent secondary outcomes. The intervention includes modules on debt management, impulse control, gambling-specific cognitive biases, self-esteem, social competence, sleep hygiene, mindfulness and positive activities.

**Discussion:**

This study is one of the first investigations of Internet-based self-help programs in a sample of problematic gamblers. Self-guided Internet-based interventions represent a promising possibility to narrow the existing treatment gap while saving expensive and scarce resources (e.g., psychotherapists). The expected findings will add substantial knowledge in the development of effective Internet-based treatments for individuals with gambling problems. The empirical and clinical implications (e.g., broader use and promotion of such interventions in the future) and the limitations of the study will be discussed.

**Trial registration:**

ClinicalTrials.gov, NCT03372226. Registered on 13 December 2017.

**Electronic supplementary material:**

The online version of this article (10.1186/s13063-019-3176-z) contains supplementary material, which is available to authorized users.

## Background

Many people dream of a big win and according to a survey of the German Federal Center for Health Information [1] 77.6% of the 16–70 year-old German population have had a gambling experience at least once in their life. For some, this dream turns out terrible and what once used to be an entertaining hobby becomes a profound problem. Slot-machine gambling has been described as the most harmful and addictive gambling form, which is also reflected by the fact that most of those seeking help report this form of gambling [2, 3].

Pathological gambling is characterized by persistent and recurrent problematic gambling behavior leading to clinically significant impairment or distress [4]. The individuals affected experience a loss of control over their gambling activity and have persistent thoughts of past gambling experiences, upcoming ventures and every possible way to obtain money. More and more money is invested in order to experience the desired excitement or to chase losses. The urge to play - despite obvious negative consequences - is often driven by a variety of gambling-specific cognitive biases such as illusion of control (perceiving control over an uncontrollable event), gambler’s fallacy (overestimating the probability of predicting an event), chasing (the belief that after a significant loss, money can only be recovered through continued gambling), superstitious beliefs (e.g., assigning lucky attributes to objects, behaviors, etc.), misattributions (external and internal) and magical thinking (the belief that behaviors that are not causally related to the outcome can influence the probability of winning) (for an overview of gambling-specific cognitive biases see [2]). There is evidence that the presence of those cognitive biases is involved in the maintenance of problematical and pathological gambling behavior [5, 6]. Therefore, the biases should be more thoroughly addressed and focused on in the treatment of gambling disorders, for example by using strategies referred to as cognitive restructuring (CR) that help clients understand that their thoughts are irrational [7].

Furthermore, depressive symptoms are associated with problematic and pathological gambling. Although there is consensus that depressive symptoms are often observed in pathological gamblers, the exact causal relationship between both is disputed. Several models for categorizing gamblers into types have been proposed [8–10]. Each of these models describes at least two types of gamblers - those who gamble to reduce preexisting negative emotions and those who develop depressive symptoms in response to gambling-related problems such as financial difficulties [9]. As one to two thirds of the individuals affected appear to have comorbid depressive symptoms, they should definitely be addressed in therapy [11].

Despite numerous negative consequences and suffering, only a small fraction of those affected receive professional treatment [12] and attrition rates are high for those who start therapy [13, 14]. There is evidence on the effectiveness of psychological treatments for pathological gambling [15], with cognitive behavioral therapy appearing to be the most effective [16, 17]. However, conventional “face-to-face” therapies do not seem suitable to fill the large treatment gap [12], possibly because the treatment barriers to those forms of therapy are too high, so alternative possibilities must be considered.

Internet-based interventions have been investigated and evaluated in recent years in many studies of different mental disorders, with promising outcomes [18–20]. Benefits of Internet-based interventions include its anonymity and privacy, low costs, flexibility and accessibility [21]. This enables them to overcome treatment barriers of conventional therapies such as fear of stigma, shame and geographical or time limitations. Internet-based intervention may be guided or self-guided (unguided). Guided interventions are therapist-supported (e.g., by e-mail or telephone support), whereas self-guided interventions do not provide individual support by a trained person or psychotherapist. Studies on guided Internet-based interventions consistently report greater effect sizes than unguided Internet-based interventions [22]. Moreover, a recent meta-analysis that compared guided Internet-based interventions with face-to-face cognitive behavioral therapy (CBT) found comparable effect sizes [18]. However, smaller effect sizes in studies of self-guided Internet-based interventions nevertheless demonstrate their effectiveness [23]. Although they are less effective than guided Internet-based interventions, they have some advantages as they are more cost-effective, resource-efficient and flexible. As adherence is a problem in self-guided Internet-based interventions, it is necessary to provide strategies that enhance adherence [24]. According to a review [25], it seems that sending e-mail reminders and presenting information in textual format (instead of non-textual such as audio/video format) contributes to treatment success.

The first attempts to investigate Internet-based interventions for pathological gamblers have been made in recent years [26]. One study tested the effectiveness of an Internet-based self-help program with weekly telephone support and e-mail contacts in a sample of pathological gamblers with no comorbid severe depressive symptoms and found positive changes in pathological gambling, anxiety, depression and quality of life [27]. A randomized controlled trial (RCT) tested the efficacy of three modalities of Internet-based psychotherapy (three conditions with or without guidance and a control condition), among problem gamblers participating in online poker [28] but did not find a significant difference between the groups in treatment outcome. Guidance here means human support in the form of weekly e-mails with personalized CBT. In all groups there were high attrition rates (83%); interestingly, the attrition rate was higher in the group receiving guidance (95.3% after 6 weeks, 97.3% after 12 weeks) compared to the other experimental groups, tentatively indicating that guidance has adverse effects in Internet-based interventions for problem gamblers. In a pilot study, we investigated whether a self-help online program for depressive symptoms “Deprexis” has positive effects on depressive and gambling-related symptoms [29]. This intervention led to a significant reduction in depressive symptoms and gambling-related symptoms, compared to a control group. However, the results gave rise to the hypothesis that treatment effects are likely augmented if the program is tailored to the specific needs of problem gamblers.

The efficacy of Internet-based interventions has been shown in many trials in other psychiatric disorders and the first results from these studies of pathological gambling are promising. However, studies in this particular field, especially randomized controlled studies, are rare. Building upon the results of the pilot study, our study group developed an Internet-based intervention, called “Restart”, that addresses gambling-related and emotional problems. The Internet-based intervention is accompanied by a smartphone application (app) that sends daily reminders, with small exercises that can be easily integrated into everyday life, to increase therapeutic success. A review has indicated the efficiency of smartphone-supported self-help [30].

The aim of the study is to evaluate the efficacy and acceptance of the Internet-based intervention, Restart, which is aimed at treating gambling-related and emotional problems. We expect that the Internet-based intervention will lead to a significant reduction in pathological gambling (primary treatment target) as measured by the Pathological Gambling Adaptation of Yale-Brown Obsessive Compulsive Scale (PG-YBOCS), gambling-specific cognitive distortions (measured by the Gambling Attitudes and Beliefs Survey (GABS)) and depressive symptoms (measured by the Patient Health Questionnaire - 9 (PHQ-9) depression module) when compared with a control group that receives no treatment.

## Methods

### Study design

The self-help program is evaluated in the framework of a RCT with parallel assignment to two conditions. The intervention group receives Restart over a period of 8 weeks and will be compared with a wait-list control group, which receives full access to the program following the post-intervention assessment. There are two assessment points (baseline and post intervention), where data are obtained by an Internet survey using Unipark®. At baseline, sociodemographic and psychopathological data are assessed; at the post-intervention assessment, psychopathological data and subjective evaluations of the Internet-based intervention (only for the Restart intervention group) are assessed. Within the online baseline assessment, participants are screened for inclusion and exclusion criteria before randomization. All participants will be invited to participate in the post-intervention assessment 8 weeks after the baseline assessment. As an incentive, the completion of the follow-up assessment will be rewarded with a 20 Euro Amazon voucher and all participants will receive access to another Internet-based training intervention to reduce the problematic gaming behavior (retraining). See Fig. 1 for a schedule of enrollment, interventions and assessments (SPIRIT).

**Fig. 1 Fig1:**
[figure not shown]
Standard protocol items: recommendation for interventional trials (SPIRIT) timeline. PG-YBOCS, Pathological Gambling Adaption of Yale-Brown Obsessive-Compulsive Scale; SOGS, South Oaks Gambling Screen; PHQ-9, Patient Health Questionnaire-9; GABS, Gambling Attitudes and Beliefs Survey; WSQ, Web Screening Questionnaire

### Sample size

The sample size was calculated using G*Power [31], which indicated an entire sample size of 90 to detect a medium effect of *d* = 0.5, with α = 0.05 and power of 0.80 for analysis of covariance (ANCOVA). Based on previous studies of adherence in Internet-based interventions [32, 33] and among pathological gamblers [34], we expect a dropout rate of 50%. Taking this into account, the total sample size should be 136 with 68 participants in each condition.

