### Statistical analyses

Both the intention-to-treat (ITT) and per-protocol samples will be analyzed using linear mixed-model repeated measures ANCOVA with pre-to-post intervention time as the within-group factor, condition as the between-group factor and baseline scores as the covariate. Baseline differences between the two groups will be assessed using the independent samples *t* test for continuous variables and the chi-square test for categorical variables. Missing values for ITT analyses will be imputed using two different methods: (1) maximum likelihood estimation and (2) multiple imputation. In addition, we will conduct an exploratory moderation analysis to see which factors potentially have a moderating influence on symptomatic improvement using the SPSS macro PROCESS (developed by A. Hayes).

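### A total of 90 does not follow from d = 0.5, α = 0.05, 80% power and ANCOVA: those inputs give 128, and 90 needs d = 0.6 or an unstated correlation of about 0.55

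*Protocol article*

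**What the plan says.** The Sample size section of the protocol article names its software ("The sample size was calculated using G*Power [31"), its result and effect ("an entire sample size of 90 to detect a medium effect of" d = 0.5), and its error rates and test ("with α = 0.05 and power of 0.80 for analysis of covariance (ANCOVA"). The section then allows for 50% dropout and concludes that "the total sample size should be 136 with 68 participants in each condition".

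The remaining inputs are elsewhere in the article. Study design describes an "RCT with parallel assignment to two conditions". Statistical analyses specifies "condition as the between-group factor and baseline scores as the covariate". No baseline-to-post correlation, R², one-sided test or second effect size is given anywhere.

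**The concern.** The sentence prints effect size, α, power, test, software and answer together, so it can be checked, and 90 looks too small. A two-group comparison at d = 0.5 with 80% power and two-sided α = 0.05 needs roughly 64 per arm, not 45, unless the covariate is credited with removing a good part of the variance.

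This is the only power statement in the article, and it supports the test of the primary outcome, change in PG-YBOCS. The enrolment target of 136 is built on it. If 90 really belongs to a larger effect, the trial is described as able to detect a medium effect when it is not, and a null result could be misread as evidence against one.

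**Working it through.** **Inputs.** From Sample size: d = 0.5, α = 0.05, power 0.80, ANCOVA, equal arms. From Study design: two groups. From Statistical analyses: one covariate, the baseline score. The article does not state sidedness; the ANCOVA F test is non-directional.

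**Formula.** For two equal groups f = d/2. Power is the upper tail of a non-central F with df1 = 1, df2 = N − 2 − 1 = N − 3 and non-centrality λ = N·f², beyond the central F critical value at α. This is the fixed-effects ANCOVA calculation in G*Power.

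**Reproducing 90.** With f = 0.30 (d = 0.6), λ = 90 × 0.09 = 8.10, df2 = 87 and power is 0.804. At N = 89 it is 0.799, so 90 is exactly the smallest N for d = 0.6.

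**The stated inputs.** f = 0.5/2 = 0.25, so f² = 0.0625.

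| N | λ = N × 0.0625 | df2 | Power |
|---|---|---|---|
| 90 | 5.625 | 87 | 0.650 |
| 127 | 7.94 | 124 | 0.798 |
| 128 | 8.00 | 125 | 0.801 |

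The required total is 128 (64 per arm), which is 38 more than stated. The normal approximation gives 126.

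**Other readings of the same sentence, at d = 0.5.**

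- One-sided α = 0.05: N = 101 (102 for equal arms). Power at 90 is 0.76.
- No covariate: N = 128.
- Repeated-measures, between-groups factor, f = 0.25: N = 66, 84, 98 and 110 for correlations 0, 0.3, 0.5 and 0.7. This passes through 90 only at an unstated correlation between 0.3 and 0.5.
- Repeated-measures, group-by-time interaction, f = 0.25: N = 66, 46, 34 and 22 for the same correlations.
- Change score: 90 needs a correlation of about 0.65.
- One-sided ANCOVA: 90 needs a correlation of about 0.35.
- Two-sided ANCOVA with d on the raw SD scale: the residual variance shrinks by 1 − ρ², so f becomes 0.25/√(1 − ρ²). Setting this to 0.30 gives ρ = √(1 − (0.25/0.30)²) = 0.553. At ρ = 0.55, f = 0.299, N = 90 and power is 0.802.

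No reading gives 90 without an input the article does not state.

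**Power for d = 0.5 (raw scale, two-sided ANCOVA).** The correlations are assumptions, shown as a range. The 68 column is 136 × (1 − 0.50).

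| ρ | N needed | Power at 90 | Power at 68 |
|---|---|---|---|
| 0 | 128 | 0.65 | 0.53 |
| 0.3 | 117 | 0.69 | 0.57 |
| 0.5 | 97 | 0.77 | 0.65 |
| 0.55 | 90 | 0.80 | 0.68 |
| 0.7 | 67 | 0.91 | 0.81 |

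**The case against.** The strongest reply is that ANCOVA was named for a reason. If d = 0.5 is the raw standardised difference, N depends on the baseline-to-post correlation, and about 0.55 gives exactly 90. That value over 8 weeks is not implausible on its face, and a short journal paragraph may have dropped it. On this view the text shows an unreported assumption, not a wrong number, and it does not prove that f = 0.30 was entered.

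Much of this stands. There are two exact routes to 90 under a two-sided ANCOVA, and the article does not reveal which was taken. It does not rescue the sentence, though. The correlation is the input that turns 128 into 90, so an article that prints the other inputs with the answer and omits this one prints inputs and an output that conflict. The article also credits 90 to G*Power, whose ANCOVA routine has no field for a correlation, so this route would have needed f to be adjusted by hand first.

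Two further points are fair. The power at 68 completers mixes in a separate problem, the step from 90 to 136, so the consequence of this point alone is the power at 90. And nothing here touches type I error, the endpoint or the analysis model. The issue is whether the power claim is true as written.

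**Conclusion.** The concern holds. The inputs printed in Sample size require 128 participants, not 90, and 90 gives power of 0.65 for d = 0.5. This rests on a two-sided F test, equal arms, one covariate and no variance reduction beyond what is already in d. If d is on the raw scale, power at 90 runs from 0.65 at ρ = 0 to 0.80 at ρ = 0.55, so there is no shortfall at 90 if a correlation that high was assumed and is borne out. What is established is that 90 belongs either to d = 0.6 or to d = 0.5 with an assumption the article does not state. It should be corrected, because it is the trial's only power statement. Correcting the dropout allowance alone would leave this inconsistency in place.

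**What to change.** Correct the sentence in Sample size in one of two ways, according to what was actually done:

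1. State that 90 analysable participants give 80% power for d = 0.6 (f = 0.30), two-sided α = 0.05, ANCOVA with one covariate; or
2. State that d = 0.5 is the unadjusted standardised difference and that a baseline-to-week-8 correlation of about 0.55 is assumed, with the reason for that value.

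In both cases add the power at the number of completers expected. At 68 completers it is 0.68 for d = 0.5 with ρ = 0.55, and also 0.68 for d = 0.6 with no further adjustment, since f is almost the same (0.299 against 0.30).

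The cost is a revised sentence, which can go in the separate amendment that Trial status provides for. Enrolment, randomisation and analysis do not change. The price is that the detectable effect becomes less favourable or an assumption becomes visible.

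### The 50% dropout allowance was added to 90 rather than divided out: 136 randomised leaves 68 completers, not 90, so the stated 80% power is not delivered

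*Protocol article*

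**What the plan says.** In the protocol article, Methods, Sample size, the G*Power calculation is reported as one "which indicated an entire sample size of 90 to detect a medium effect". That effect is a standardised difference of 0.5, tested by ANCOVA at the 5% level with 80% power. The next step is the allowance for loss: "we expect a dropout rate of 50%. Taking this into account, the total sample size should be 136 with 68 participants in each condition". The Method part of the abstract repeats the result: "a total of 136 participants is planned".

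Three other sections bear on the point. Study design has only two assessments, baseline and one at 8 weeks. Statistical analyses plans intention-to-treat and per-protocol analyses, with missing values in the former handled by maximum likelihood and by multiple imputation. Randomization uses blocks of four, and 136 is a multiple of four. No section gives a different dropout rate or another reason for 136.

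**The concern.** A dropout allowance should leave the required number in the analysis after the expected loss. If half are lost, the number randomised must be twice the number required. Here it is only about one and a half times that number, so under the plan's own dropout assumption the analysis falls short of the 90 on which the power rests.

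This paragraph is the only justification given for the size of the trial. If it stands, a non-significant result on the PG-YBOCS would be read as coming from a trial with 80% power when, at the expected dropout, it has less.

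**Working it through.** **Inputs.** From Sample size: 90 required, d = 0.5, α = 0.05, power 0.80, dropout 50%, total 136 (68 per arm). From Study design: one post-baseline assessment.

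**Reproducing 136**
- Adding the percentage: 90 × (1 + 0.5) = 135, rounded up to 136 for equal arms. This matches.
- Dividing by the share retained: 90 / (1 − 0.5) = 180. This does not match.

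**What 136 delivers**
- Completers at 50% dropout: 136 × 0.5 = 68, or 34 per arm. Shortfall: 90 − 68 = 22.
- Dropout at which 136 still leaves 90: 1 − 90/136 = 0.338, or 33.8%.

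**Power at 68.** Two-group ANCOVA with one covariate, non-central F with 1 and N − 3 degrees of freedom, non-centrality λ = N × f², and f = d/2 for equal arms.

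The stated d = 0.5 is f = 0.25. With no gain from the covariate, that effect needs N = 128, not 90. The figure of 90 comes out with f = 0.30, or with d = 0.5 and a baseline-to-post correlation of about 0.55: f² = 0.0625 / (1 − 0.55²) = 0.0896, so f ≈ 0.30. The article states neither. Power is therefore shown on both bases.

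| Basis | Power at N = 90 | Power at N = 68 |
|---|---|---|
| 90 accepted: f = 0.30 (λ = 8.10 and 6.12) | 0.804 | 0.683 |
| 90 accepted: f set to give exactly 0.80 at 90 (f = 0.299) | 0.80 | 0.679 |
| d = 0.5, no covariate gain: f = 0.25 (λ = 5.625 and 4.25) | 0.65 | 0.53 |
| d = 0.5, assumed correlation 0.5 | 0.77 | 0.65 |
| d = 0.5, assumed correlation 0.6 | 0.83 | 0.72 |
| d = 0.5, assumed correlation 0.7 | 0.91 | 0.81 |

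The last row does not rescue the plan: at a correlation of 0.7 the required number would have been 67, not 90. The effect detectable with 80% power at 68 completers is d = 0.69 on the covariate-adjusted scale, against about 0.60 on the same scale at 90.

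**The case against.** The strongest objection concerns what dropout means. The 50% rests partly on studies of adherence, everyone is invited to the 8-week survey, and completing it earns a voucher. Someone who stops using the programme can still supply the outcome and count in the intention-to-treat analysis. If all 136 did so, power would be 0.825 even at f = 0.25. But the paragraph inflates the sample for this rate, which makes sense only if dropouts are lost to the analysis, and the Discussion also ties drop-out to assessments.

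A second defence is that the planned missing-data methods recover the loss. With a single post-baseline assessment and no auxiliary variable named, a participant who misses it adds essentially no information on the treatment effect.

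Two criticisms of the size do stand:
- The 0.68 is conditional on accepting 90, because f = 0.30 is back-calculated and not stated in the article.
- The 0.53 is not due to the dropout step alone. Without covariate gain, power at 90 is already 0.65, so of the fall from 0.80 to 0.53 about 0.15 precedes any dropout and about 0.12 comes from having 68 instead of 90. How 90 follows from d = 0.5 is a separate question.

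The slip biases neither the estimate nor the type I error. It affects the power claim and the reading of a null result.

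**Conclusion.** The sample-size paragraph is wrong as written. Its three figures (90 required, 50% lost, 136 randomised) cannot all hold: 90 with 50% loss needs 180, and 136 with 50% loss leaves 68. Taking 90 at face value, the dropout step alone lowers power from 0.80 to about 0.68 and raises the type II error from 20% to about 32%. Without covariate gain, power is 0.53. Both figures assume that the 50% are lost to the outcome assessment, which is how the plan uses the rate.

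This must be corrected, because it is the stated basis for the size of the primary comparison.

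**What to change.** Amend the Sample size paragraph and leave enrolment as it is. Either of these statements would be correct:

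- 136 randomised with 50% dropout is expected to leave 68 analysable participants, with power of about 0.68 if 90 is accepted as the number for 0.80. If the 0.53 for d = 0.5 without covariate gain is also printed, say that 90 itself gives 0.65 on that basis.
- 136 randomised delivers the required 90 only if dropout does not exceed 33.8%.

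The abstract gives only the total of 136, so its number need not change. The corrected power should be used when a null result is interpreted.

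The cost is one paragraph in an amendment, which Trial status already provides for, and a less favourable power statement. No additional participants are needed. Restoring 80% power at 50% dropout would instead mean randomising 180, which is 44 more, and that only if 90 is right.
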